
**Figure 2 F2:**
[figure not shown]
Overview of blood biomarkers. Laboratory parameters reflecting biomarkers of chronic heart failure; CRP, C-reactive protein.

### Adverse Events and Safety Considerations

In both groups (MCT and HIT) adverse events (AE) and serious AE will be recorded. All potential cardiovascular events will be considered to be serious AEs (e.g., atrial and ventricular arrhythmia, unstable angina pectoris, clinical worsening of HF requiring hospitalization or intensified diuretic therapy, cardiovascular death) and will be immediately treated, recorded and/or discussed in detail to plan further procedures. If clinically indicated, laboratory parameters (kidney and liver values, International Normalized Ratio, hematology, etc.) will be measured and the patient's personal cardiologist will be informed to discuss further procedures.

Safety and adherence after end of the study will be checked during follow-up calls. Patients will be referred to adequate long-term rehabilitation settings (e.g., ambulant cardiovascular rehabilitation, KARAMBA; or the Swiss Physical Activity Promotion in Primary Care System, PAPRICA).

### Randomization

Patients will be randomly allocated to either the intervention or the control group in a 1:1 ratio stratified by gender. Randomization will be done using a computer-based system implemented in the Castor software (Castor, Amsterdam, Netherlands). The randomization procedure includes a minimization algorithm. The randomization procedure is implemented in the online electronic-data-capture system provided by Castor. Only authorized study personnel will have access to the randomization tool and can assign a treatment to a new study patient. Due to the minimization algorithm, the allocation sequence is totally concealed until randomization is carried out.

### Blinding

It is not possible to blind patients or investigators performing the randomization and training sessions. Therefore, un-blinding procedures are not applicable. However, data analysis will be performed by investigators blinded for patient data and allocation to HIT, respectively, MCT.

### Intervention

All patients will perform a 12-week training program 3 times per week on a bicycle ergometer (Ergoselect 200, Ergoline, Bitz, Germany), Figure 3. During training, patients will wear the Sense system (CSEM, Neuchâtel, Switzerland). The Sense system measures heart rate, breathing rate and a 1-channel ECG, which can be displayed live on a tablet to control exercise intensity and heart rhythm. If heart rate is too high or too low, intensity is adjusted. The Borg 6-to-20 Scale will be used to assess the rate of perceived physical exertion during and after each training session. HIT and MCT are designed to achieve a similar energy expenditure (isocaloric design). Every training session will be supervised and controlled by sports scientists to keep patients train in the planned intensity in order to avoid overlap of training intensities of HIT and MCT.

**Figure 3 F3:**
[figure not shown]
Overview of the endurance-strength training protocols. Training protocol for HIT and MCT during the 12-week intervention period. W-up, warm-up; HR_peak_, heart rate peak; 5RM, 5-repetition maximum; RT, resistance training; HIT, high-intensity interval training, c-down, cool-down; MCT, moderate continuous training.

#### HIT Group

During the 12-week intervention period, we will use an adapted version of the classical 4 x 4 min protocol of Wisloff et al. (2007) with increasing HIT interval frequency and duration from week 1–9 without any further increase until week 12. From week 1 to 8, resistance training based on the intervention study of Beckers et al. (2008) and recent evidence from literature review (Giuliano et al., 2017) with decreasing volume and current recommendations (Schindler et al., 2019) will be conducted: Since patients might not be able to sustain a traditional 4-min HIT protocol (Schindler et al., 2019), we decided to increase the intensity from week to week. Patients will warm up for 5 min at moderate intensity (60–70% of HR_peak_, Borg 11–13) before resistance training and 5 min before cycling intervals with increasing time from 1 to 4 min and increasing frequency from 2 to 4 intervals at high intensity (85–95% of HR_peak_, Borg 15–17). Each interval will be separated by a 3 min active pause at 60–70% of HR_peak_ (Borg 11–13). The training session will end with a 3 min cool-down at moderate intensity (60–70% of HR_peak_). Resistance training will consist of four strength exercises (Leg Press, Leg Curl, Leg Extension, and Calf Raises) on weight machines (Cybex, divison of Lumex Inc, NY, USA), with 2 × 15 repetitions per set at 60% of the five repetition maximum (5RM) from week 1 to 4 and 2 × 10 repetitions per set at 80% of the 5RM from week 5 to 8. There will be no resistance training from week 9 to 12. Total exercise time will be 38 min. Resistance exercise shall be performed in order to prepare for the intensive endurance parts. Interference effects of strength before endurance training seem negligible for subjects with HF (Hickson, 1980; Coffey and Hawley, 2017; Vechin et al., 2021).

#### MCT Group

Patients perform the same strength exercises and then cycle continuously over a period of 12 weeks, increasing from initial 17 to 26 min from week 1 to 8 and 44 min from week 9 to 12 at 60–70% of the HR_peak_.

### Criteria for Modifying or Discontinuing the Intervention

Workload of the bicycle ergometer will be continuously adjusted in order to maintain a constant relative exercise intensity throughout the 12-week training period according to the protocol (Wisloff et al., 2007). Termination criteria include intolerable symptoms during exercise training [e.g., severe transient dyspnoea, dizziness, systolic blood pressure >260 mmHg and/or diastolic blood pressure >115 mmHg, frequent arrhythmias, palpitations (>30 s)] as well as subjective physical or mental overload (e.g., strong discomfort, excessive stress reactions, fatigue), which prevent the patient from further participation.

Based on the current epidemiological situation and regulations in Switzerland, it seems very likely to be able to offer continued training during another COVID-lockdown.

### Compliance With the Study Intervention

Good compliance will be ensured by friendly research staff, motivating training units and improving health outcomes, such as better QoL. In case a patient will miss a training session, it will be rescheduled, if possible. A compliance of 80% (29 sessions) will be required to be considered in the analysis of the per-protocol set (PPS).

### Concomitant Treatments

Concomitant treatments or medication considered necessary by the treating physicians are permitted. However, if the ability to exercise is affected in case of worsening HF (e.g., cardiac decompensation, NYHA IV) or any new diagnosis of concomitant disease (e.g., cancer, pulmonary hypertension, trauma, and so on), patients will be excluded from the study and will not be allowed to resume the study procedures at a subsequent date.

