### Statistical Methods and Data Analysis

The full analysis set (FAS) will include all patients randomized to the trial, regardless of compliance. The PPS will include all patients from the FAS, who had a 12-week post-intervention visit and who complied with their assigned treatment.

The primary analysis will be done on the FAS and based on the intention to treat principle. Patients will be analyzed according to the group to which they were assigned. Missing values in the primary endpoint will be imputed using multiple imputations via chained equations based on baseline characteristics. An ANCOVA approach will be taken: a linear regression model will be used to model patient VO_2peak_ at post-intervention as outcome, with the baseline value as an independent covariate. As an explorative analysis, the association of tHb-mass and patient type, as well as their combined effects on VO_2peak_ will be examined using multiple regression models or other methods for estimating causal effects. As a safety analysis, the number and type of AEs will be summarized and reported per group. In addition, the number of non-compliant patients and their baseline characteristics compared between treatment groups will be summarized.

Confounding variables such as baseline patient characteristics (e.g., age, BMI, smoking/drinking), comorbidities, medication, and baseline fitness level will be accounted for during regression analyses.

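### Patients who deteriorate after randomisation leave the study, so their 12-week VO2peak is not collected and is imputed from baseline as if they had not deteriorated

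*Protocol article*

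**What the plan says.** Four sections of the protocol article bear on this.

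- **Concomitant Treatments.** The rule applies "if the ability to exercise is affected in case of worsening HF (e.g., cardiac decompensation, NYHA IV) or any new diagnosis of concomitant disease". In that case "patients will be excluded from the study and will not be allowed to resume the study procedures at a subsequent date". The text does not say whether this ends training, assessments, telephone follow-up, or all three.
- **Description of the Study Procedures.** After the last training session, the study measurements are done again within a week in every patient of both arms. Telephone interviews follow at 6 months and at 1, 2 and 3 years after the last study visit.
- **Statistical Methods and Data Analysis.** "The full analysis set (FAS) will include all patients randomized to the trial, regardless of compliance". "The primary analysis will be done on the FAS and based on the intention to treat principle". For gaps in the endpoint: "Missing values in the primary endpoint will be imputed using multiple imputations via chained equations based on baseline characteristics". The per-protocol set is narrower: "The PPS will include all patients from the FAS, who had a 12-week post-intervention visit and who complied with their assigned treatment".
- **Adverse Events and Safety Considerations.** Serious events are recorded in both arms and include "clinical worsening of HF requiring hospitalization or intensified diuretic therapy". The statistical section adds: "As a safety analysis, the number and type of AEs will be summarized and reported per group".

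**The concern.** The trigger for exclusion is close to the outcome itself. The rule acts when the ability to exercise is impaired, and the primary endpoint is exercise capacity. The patients it removes are therefore likely to have low 12-week VO2peak for reasons that arose after randomisation. An imputation that uses baseline characteristics only cannot see those reasons. It gives such a patient a value typical of patients who looked similar at baseline and completed the trial.

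Unequal exclusion between arms is possible. The arms train at different intensities (85-95% against 60-70% of peak heart rate), the staff who supervise training know the allocation, and whether the ability to exercise is affected is a judgement. If exclusions or the degree of deterioration differ by arm, the estimated HIT minus MCT difference is biased. If they do not differ, the difference is unbiased, but the mean in each arm is still too high.

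**Working it through.** **1. Follow one patient through the text.** A randomised patient decompensates in week 6 and can no longer exercise as planned.

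- Concomitant Treatments: the patient leaves the study and may not resume its procedures. The post-intervention visit, where VO2peak is measured, is a study procedure.
- Description of the Study Procedures: measurements are repeated in all patients. For this patient the two sections disagree.
- Statistical Methods: the patient stays in the full analysis set, in the assigned arm, with VO2peak imputed from baseline.
- Per-protocol set: the patient is absent, having no 12-week visit. That analysis cannot show the effect of the deterioration either.

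**2. The plan's own figure.** Inputs from Sample Size: difference 2, SD 4.2, correlation 0.7, alpha 0.05 (two-sided assumed), power 80%, dropout 10%.

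- t-test: 70.2 per arm, rounded up to 71, so 142 in total.
- ANCOVA formula: 142 x (1 - 0.7^2) + 2 = 74.4, so 75, or 76 for equal arms.
- Dropout: 75/0.9 = 83.3, so 84; 76/0.9 = 84.4, so 85.

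The plan states 77 evaluable and 86 recruited, so it reproduces to within 2 patients. The present point changes none of these figures. The 10% allowance, about 9 of 86 patients, protects power; it does not address why the values are missing.

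**3. Size of the bias.** Let pH and pM be the shares excluded under this rule in HIT and MCT, and let D be the amount by which their true 12-week VO2peak lies below the imputed value, taken as equal in both arms. Each arm's mean is overstated by p x D, so

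bias in (HIT - MCT) = (pH - pM) x D.

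The document gives no value for pH, pM or D. All values below are assumptions, with D from 1 to 4 ml/min/kg.

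| pH | pM | Bias at D = 1 | Bias at D = 4 |
|---|---|---|---|
| 5% | 10% | -0.05 | -0.20 |
| 5% | 5% | 0 | 0 |
| 10% | 10% | 0 | 0 |
| 10% | 5% | +0.05 | +0.20 |
| 10% | 0% | +0.10 | +0.40 |
| 15% | 5% | +0.10 | +0.40 |

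A positive sign favours HIT. In the 10%/10% row the between-arm bias is zero, yet each arm's mean is overstated by 0.10 to 0.40.

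**4. Scale.** Against the target of 2, the range is -0.2/2 = -10% to +0.4/2 = +20%. With the plan's inputs, the standard error of the adjusted difference is about 4.2 x sqrt(0.51) x sqrt(2/38.5) = 3.00 x 0.228 = 0.68. A bias of 0.4 is therefore about 0.6 standard errors, and 0.2 about 0.3.

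The upper end is demanding. The 15%/5% row averages 10%, so it uses the whole dropout allowance for this one cause; the 10%/0% row puts every exclusion in one arm.

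**The case against.** The strongest reply is that the plan is workable as written. Several stronger readings are tempting, and the document does not support them.

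- **That the rule contradicts the intention-to-treat analysis set.** It does not. The full analysis set keeps every randomised patient, and a missing endpoint is imputed. The disagreement is with the section that repeats measurements in all patients; the harm to the intention-to-treat estimate comes from what is imputed.
- **That any worsening or any new diagnosis leads to exclusion.** The rule is conditional on the ability to exercise being affected. Some of its examples, such as cancer or trauma, have no stated link to the training arm.
- **That harm is hidden.** Adverse events are recorded in both arms and reported per group, so an excess of decompensation in one arm would be visible there. It would not be visible in VO2peak.
- **That long-term follow-up of these patients is lost.** The text bars study procedures and does not say whether the telephone calls stop. Loss is possible but not stated.

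Two further objections carry weight. Some of these patients could not perform a maximal exercise test at 12 weeks under any retention rule, so better wording recovers only part of the missing data. A missing-not-at-random sensitivity analysis, and detail on withdrawal, may also stand in the full protocol or an analysis plan that is not shown. The point does not rest on their absence. It rests on two rules the article does state: exclusion from the study, and imputation from baseline characteristics.

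**Conclusion.** The point holds in a limited form. Followed as written, the text fails to collect the primary endpoint in patients who have deteriorated and replaces it with a prediction that ignores the deterioration. That weakens the intention-to-treat estimate, and the passages on exclusion, repeat measurement and imputation need to be reconciled.

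The size is not known. Under the assumptions above the bias in the difference runs from about -0.2 to +0.4 ml/min/kg. It is zero when exclusions and deterioration are equal in the two arms. A reader might infer that the plan favours HIT, for instance by assuming 2 to 4 of 43 HIT patients excluded, none in MCT, and a 4-unit shortfall: (2/43) x 4 = 0.19 to (4/43) x 4 = 0.37, or 9% to 19% of the target. The arithmetic is right, but the one-sided split is an assumption. Nothing in the document supports that direction over the other.

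**What to change.** Reconcile Concomitant Treatments, Description of the Study Procedures and Statistical Methods, leaving the clinical criteria for stopping training as they are.

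1. State that a patient who meets those criteria stops the training intervention and stays in the study for outcome assessment unless consent is withdrawn. This covers the post-intervention visit at the originally scheduled time with whatever assessments are feasible, the telephone follow-up, and adverse event recording. Whether an exercise test is feasible remains a clinical decision. Fixing the visit date also matters because the text ties the visit to the last training session, which for these patients may come early.
2. State that these patients remain in the full analysis set, and record the reason for each missing VO2peak.
3. Add one delta-adjusted (missing-not-at-random) sensitivity analysis. For patients whose VO2peak is missing after such an event, lower the imputed value by a decrement taken from a range fixed before the data are seen, and let the decrement differ between arms. The 1 to 4 ml/min/kg used above, half to twice the target difference, is one possible range, but the choice needs its own justification.

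The cost is a change of wording, a few follow-up visits after training has stopped, and one extra analysis. The wording matters most while patients are still in the trial, since outcomes that were not collected cannot be recovered at analysis.

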### Sample Size

We use a closed form formula to assess the sample size, as implemented in the R function “power.t.test()”. This provides us a sample size for comparison of two independent groups. Borm et al. (2007) showed that including the baseline value as a covariate in an ANCOVA design as planned here, can reduce the required sample size while maintaining power. Accordingly, the required sample size would be N_total_ = N_t−test_
^*^ (1 – ρ^2^) + 2, where ρ is the within patient correlation between baseline values and follow-up. To obtain realistic assumptions on the baseline VO_2peak_ distribution required for the sample size calculation, we performed a meta-analysis of five research papers (Kitzman et al., 2010, 2013; Edelmann et al., 2011; Alves et al., 2012; Smart et al., 2012). The fixed effects meta-analysis suggested the standard deviation of VO_2peak_ at baseline to be 3.39 ml min^−1^ kg^−1^. For the sample size estimation, we take a slightly more conservative value, assuming baseline VO_2peak_ to have a standard deviation of 4.2 ml min^−1^ kg^−1^, ~25% higher than suggested by the meta-analysis. In addition, we assume the within-patient correlation to be 0.7 ml min^−1^ kg^−1^, which is rather low for such measurements. We set the type-I error rate, α, to 0.05, and the power of the study (1-β) to 80%. We only allow a dropout rate of 10% for the primary outcome at 12 weeks.

Under these assumptions, with a 1:1 treatment allocation ratio, 86 patients need to be recruited in order to show a minimal clinically relevant difference of 2 ml min^−1^ kg^−1^, while maintaining power for the PPS with 77 evaluable patients.

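### The 77 evaluable patients claimed for the per-protocol set are recruitment less 10% dropout, with nothing allowed for completers who miss the 29-session mark

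*Protocol article*

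**What the plan says.** Three sections of the protocol article bear on this.

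- **Sample Size.** One loss is budgeted: "We only allow a dropout rate of 10% for the primary outcome at 12 weeks". The section concludes that 86 patients are needed, "while maintaining power for the PPS with 77 evaluable patients".
- **Statistical Methods and Data Analysis.** The PPS consists of the FAS patients "who had a 12-week post-intervention visit and who complied with their assigned treatment". The same section puts the primary analysis on the FAS, by intention to treat, with multiple imputation of missing endpoints. It also plans to summarise how many patients were non-compliant.
- **Compliance With the Study Intervention.** This fixes the PPS threshold at 80% of sessions, which it gives as 29. Missed sessions are rescheduled where that can be done.

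**The concern.** The PPS has two entry conditions, a 12-week visit and enough training sessions. The sample-size calculation takes off losses for the first condition only and then attaches the result to the PPS. A patient who attends 25 sessions and returns for the 12-week exercise test has the primary outcome and is not a dropout, but is outside the PPS.

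What is at stake is a stated property of the design. A reader of the Sample Size section would take the per-protocol comparison to have at least 80% power and could give a null per-protocol result more weight than it can bear. In this trial readers are likely to look at that comparison, because the Introduction stresses that an earlier trial of the same two training modes did not deliver the planned intensities.

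**Working it through.** **Inputs, all from Sample Size unless noted**

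- Target difference 2, SD 4.2 (both ml/min/kg), baseline-to-follow-up correlation 0.7, alpha 0.05, power 80%, 1:1 allocation, dropout 10%.
- ANCOVA reduction: N_total = N_t-test × (1 − ρ²) + 2, with 1 − 0.7² = 0.51.
- Sidedness is not stated. Two-sided is assumed; it is the default of the R function named and it reproduces 86.
- Sessions: 12 weeks × 3 per week = 36 (Intervention); 0.8 × 36 = 28.8, hence 29 (Compliance With the Study Intervention).
- Non-compliance rate among completers: not given anywhere.

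**Step 1. Reproduce 86.** The two-sample t-test needs 70.2, rounded up to 71 per arm, so N_t-test = 142. Then 142 × 0.51 + 2 = 74.42, or 37.21 per arm, rounded up to 38. Dividing by 0.9 gives 42.2, rounded up to 43 per arm, so 86. The article does not show its rounding, but this route matches exactly. Rounding the total instead gives 75/0.9 = 83.3, so 84, which is close.

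**Step 2. Find the source of 77.** 86 × 0.9 = 77.4, so 77. Dropout is the only deduction.

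**Step 3. Compare with the PPS.** If c completers attended fewer than 29 sessions, the PPS has 77 − c patients. It has 77 only if c = 0.

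**Step 4. Power at each PPS size.** Invert the protocol's formula, N_t-test = (N − 2)/0.51, and take the t-test power at N_t-test/2 per arm.

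| PPS size | Completers lost (c) | Equivalent t-test N per arm | Power |
|---|---|---|---|
| 77 | 0 | 75/0.51/2 = 73.5 | 81.8% |
| 74 | 3 | 72/0.51/2 = 70.6 | 80.2% |
| 73 | 4 | 71/0.51/2 = 69.6 | 79.7% |
| 69 | 8 | 67/0.51/2 = 65.7 | 77.3% |
| 62 | 15 | 60/0.51/2 = 58.8 | 72.6% |

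So 80% needs 74 patients, and 77 − 74 = 3 non-compliant completers (3/77 = 3.9%) can be absorbed.

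**Step 5. Sensitivity to the method.** A direct ANCOVA calculation, with residual SD 4.2 × √0.51 = 3.00 and N − 3 degrees of freedom, gives 82.3% at 77, 80.2% at 73, 79.7% at 72, 77.9% at 69 and 73.3% at 62. The tolerance becomes 4 instead of 3, and the conclusion is the same.

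**Step 6. Illustrative range.** The rates here are assumptions. With 5% of completers non-compliant, 77 × 0.95 = 73.15, so 73 patients and about 80% power (79.7%). With 10%, 69.3, so 69 patients and about 77%. With 20%, 61.6, so 62 patients and about 73%.

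**The case against.** **The 10% may be meant to cover every loss from the PPS.** The sentence ties 77 to the PPS directly. Patients who stop under the discontinuation criteria or are excluded under Concomitant Treatments would often be dropouts already. Sessions are supervised and missed ones are rescheduled where possible. It follows that non-compliance among completers should be lower than non-compliance overall. But the text defines the 10% as dropout for the 12-week outcome, and a non-complier can still supply that outcome. The plan to summarise non-compliant patients shows that some are expected.

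**The inputs are conservative.** The SD of 4.2 was set above the pooled 3.39. At 3.39 the same formula gives 94.4% power with 77 patients, 91.9% with 69 and 88.7% with 62. This lowers the practical weight of the point. It does not rescue the sentence, which claims power under the stated assumptions, including 4.2.

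**Stronger readings that the document does not support.**

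- A reader might infer that the sample size is miscalculated or the trial underpowered. It is not: 86 is reproduced, and the primary analysis is on the FAS.
- A reader might infer that the FAS size is missing. The FAS is all randomised patients, and 86 is stated.
- A reader might infer that the PPS will fall well short of 80% power. That needs a non-compliance rate, and none is given. Up to about 3 non-compliant completers the claim would still come true.

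**Conclusion.** Wrong as written. The number 77 counts patients expected to have a 12-week VO2peak, not the PPS, and the claim that power is maintained for the PPS has no allowance behind it. Under the protocol's formula it holds with up to about 3 non-compliant completers out of 77 and fails beyond that. The shortfall is small at low non-compliance and grows to about 7 percentage points below 80% if one completer in five falls short.

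This rests on the protocol's own inputs, a two-sided alpha, and the reading of dropout as loss of the 12-week measurement. The 5%, 10% and 20% rates are illustrations, not estimates. The primary FAS analysis and the recruitment target are unaffected, so the point concerns an incorrect statement about a secondary analysis set.

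**What to change.** In Sample Size:

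1. State that 86 patients are randomised and that 77 are expected to have a 12-week VO2peak, which gives about 82% power on observed cases (difference 2, SD 4.2, correlation 0.7, two-sided alpha 0.05).
2. Remove the claim that power is maintained for the PPS, and describe the PPS analysis as supportive of the primary FAS analysis.
3. If PPS power is reported, give it as a range and say that the non-compliance rate among completers is assumed: for example 5%, 73 patients, about 80%; 10%, 69 patients, about 77%; 20%, 62 patients, about 73%.

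The cost is two or three sentences and a slightly less favourable stated figure for the PPS. Recruitment and the primary analysis do not change.
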